#### Participant’s perception and impact of the intervention

Descriptive statistics and inductive thematic analysis will be used to analyze responses to the closed and open-ended questions about participants’ perceptions and the impact of the workshop.

### Interim analyses {21b}

No interim analysis will be conducted.

### Methods for additional analyses (e.g., subgroup analyses) {20b}

Secondary analyses will adjust for pre-specified baseline variables in the regression models for primary and secondary outcomes. Exploratory analyses will include examining for effect modification on the outcomes between rural vs urban location of the schools, mode of workshop delivery, age, language spoken at home, gender, sexual orientation, and Aboriginal or Torres Strait Islander status.

To explore the robustness of the cost-effectiveness results, sensitivity analyses will be carried out. Both complete case analysis and intention to treat analysis will be conducted. The parameters including intervention costs or intervention pathway or proportion of adolescent males who receive the intervention will be varied in the sensitivity analysis.

### Methods in analysis to handle protocol non-adherence and any statistical methods to handle missing data {20c}

Non-compliance to the assigned intervention on the estimated intervention effect will be investigated using complier average causal effect (CACE) analysis for the primary and secondary outcomes [43].

Appropriate methods for handling the missing data will be informed by a blinded review of the data. Information on reasons for not completing the surveys and/or workshops (e.g., absent on the day, did not assent) will be collected for the students whose parents consent to the trial. Information will also be collected on the number of students who attended the workshops from Tomorrow Man. Sensitivity analyses using a pattern-mixture model will be used to assess the robustness of the missing data assumption for the primary outcome.

A statistical analysis plan detailing the additional analyses, including CACE analysis, approach for handling missing data, and sensitivity analyses, will be made available prior to the statistical analysis of the primary outcome.

### Plans to give access to the full protocol, participant-level data, and statistical code {31c}

At the end of the project, deidentified coded quantitative data collected in the questionnaires will be uploaded to the Monash University Research Repository to be held for a maximum of 5 years after the last publication from the trial researchers. Qualitative responses will not be uploaded to this repository due to the potential to identify participants. Access to the data will be determined by the researchers on a case-by-case basis and only if there is a detailed research plan and relevant ethics approvals. The study protocol is available at the Australian New Zealand Clinical Trials Registry. The full protocol and statistical code will be available by contacting the principal investigator.

## Oversight and monitoring

### Composition of the coordinating center and trial steering committee {5d}

There is no formal committee for the coordination and oversight of this trial. The principal investigator will oversee and coordinate all aspects of the trial and consult the Advisory Group at key decision points.

### Composition of the data monitoring committee, its role, and reporting structure {21a}

There is no formal committee for the monitoring of data collected as part of this trial. Data monitoring will be undertaken by a researcher supervised by the trial biostatistician who will be removed from the daily activities of the trial. Questionnaire responses will be checked to determine any problems with the data collection instruments and any unforeseen negative impacts of participation.

### Adverse event reporting and harms {22}

The potential risks of participation in this trial are minimal. The workshops are already being delivered in schools by *Tomorrow Man*. *Tomorrow Man* facilitators are experienced in working with adolescents and are also trained in suicide prevention skills. They support participants during the workshop and then provide comprehensive handover of students to school teachers and/or welfare officers at the end of each group workshop. Participation in the trial will require students to complete two questionnaires focused on help-seeking, masculinity, and factors that are protective against suicide. It is not anticipated that completion of the questionnaire will produce any risks for participants greater than inconvenience or mild discomfort. In this trial, an adverse event will be defined as a participant becoming significantly distressed as a consequence of their involvement in the trial. If any adverse events are detected in the monitoring of the data, such as open-ended responses that indicate significant participant distress, then the Monash University Human Ethics Committee will be notified and they will advise the researchers about action to address the event.

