### Criteria for discontinuing or modifying allocated interventions {11b}

There will be no modification to the interventions. Schools and participating students will be free to withdraw from the trial at any point. This will not impact on their involvement in the workshop. Students who choose not to take part in, or complete, the trial will still be able to take part in the workshop. Facilitators will monitor students for signs of distress during the workshop and the decision to withdraw students from the workshop will be made collaboratively between the facilitators and the schools. The researchers will not be involved in this process.

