## Data collection and management

### Plans for assessment and collection of outcomes {18a}

Outcome measures will be collected from students at baseline after randomization of schools. For the intervention group, data will be collected at baseline within 2 weeks of the intervention being delivered. The follow-up questionnaire will be administered 4–6 weeks after the workshop. For the waitlist control group, baseline and follow-up data collection will occur 6–8 weeks apart before the workshop is delivered.

For both groups, the baseline and follow-up questionnaires will be administered online within an allocated class time. The baseline questionnaire will include demographic questions and the measures related to the primary, secondary, and economic outcomes that are described below. The follow-up questionnaire will be a repeat of the baseline questionnaire, minus the demographic questions, with the addition of some open-ended questions for the intervention group.

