#### Participant’s perception and impact of the intervention

In addition to these standardized measures, in the follow-up questionnaire, the intervention group will be asked a set of closed and open-ended questions regarding their perceptions of the workshop (What parts did you like the most/least? Did you change your attitudes or behaviors in any of the following ways?) and the impact of the workshop on their lives (Did the workshop change your ideas about what sort of man you’d like to be? Did the workshop change the way you talk with your mates/family about personal stuff?).

The questionnaires are available from the principal investigator.

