### Data management {19}

All data will be self-report and entered by students into a secure online questionnaire that will be managed by Logicly. The questionnaires will be online and programmed with a logic that minimizes missing data by alerting participants to unanswered questions and maximizes data quality (e.g., range checks for data values). At the end of the data collection period, all data will be provided in the deidentified form to the researchers. Data will be stored in accordance with Monash University data storage policies [41].

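### Harms are to be found in questionnaire responses and reported promptly, yet the responses are released, deidentified, only at the end, and free text is collected in one arm only

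*Protocol article*

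**What the plan says.** Adverse event reporting and harms {22} gives a definition that applies to either arm: "an adverse event will be defined as a participant becoming significantly distressed as a consequence of their involvement in the trial". It then names the means of detection: "If any adverse events are detected in the monitoring of the data, such as open-ended responses that indicate significant participant distress", with notification of the ethics committee to follow so that it can advise on action.

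The data monitoring section {21a} describes the activity behind this: "Questionnaire responses will be checked to determine any problems with the data collection instruments and any unforeseen negative impacts of participation". It assigns the work as follows: "Data monitoring will be undertaken by a researcher supervised by the trial biostatistician who will be removed from the daily activities of the trial". The auditing section {23} commits the team to passing adverse events on promptly.

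On access to the data, Data management {19} states: "At the end of the data collection period, all data will be provided in the deidentified form to the researchers". Implementation {16c} puts the hand-over at the end of the trial, deidentified and blinded. Confidentiality {27} puts it after data collection has finished, again deidentified.

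On content, the assessment section {18a} makes the follow-up form a repeat of the baseline form without demographics, "with the addition of some open-ended questions for the intervention group". The section on participants' perceptions confirms that "the intervention group will be asked a set of closed and open-ended questions regarding their perceptions of the workshop".

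On distress in the workshop itself, section {11b} leaves withdrawal of a student from the workshop to facilitators and schools and adds: "The researchers will not be involved in this process".

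**The concern.** Monitoring that is meant to lead to action needs three things: someone who reads the responses while action is still possible, a way to get from a response to the student, and comparable sources in the two arms. The protocol promises the result, but its data-flow sections do not provide for the first two, and for free text they rule out the third.

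At stake is the team's ability to keep its own commitment on harms in a trial of adolescents whose subject is help-seeking and suicide prevention. A second consequence is for reporting: any count of events found in open text will come from one arm by construction, and a reader could mistake that for a difference in harm.

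**Working it through.** The protocol gives no figure for this point, so there is none to reproduce. The check sets the sections side by side and adds one date calculation.

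1. **Does anyone see response content during collection?** Sections {21a}, {22} and {23} need this. Sections {16c}, {19} and {27} each place release to the researchers at the end of the trial or of data collection. The only feed described during the trial is the data manager's weekly report in section {11c}, which covers consent, assent and survey completion by school and not what students wrote. No section gives the monitoring researcher separate access.

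2. **Is there a route back to a student?** All three release sections describe deidentified data. The data manager holds the email link, but no procedure is given for using it after a worrying response.

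3. **How long could a response wait?**
   - Start: student recruitment began in April 2021 (Study setting {9}).
   - Open-ended items appear only at follow-up, 6–8 weeks after baseline (Eligibility {10}). The first such answers therefore date from about June 2021; none can exist in April.
   - End: recruitment is to finish in October 2022 (Trial status).
   - Delay for the earliest respondents: June 2021 to October 2022 = 12 + 4 = 16 months.
   - Range: if students recruited in October 2022 are followed up 6–8 weeks later, collection ends about December 2022 and the delay is 12 + 6 = 18 months. If 2022 collection proved unnecessary, a contingency the Discussion mentions, June to December 2021 gives about 6 months. The last respondents would wait very little.

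4. **Are the sources equal by arm?** The definition in {22} covers both arms, since answering the questionnaires is itself involvement in the trial. The open-ended items are in the intervention arm's follow-up form only. With 1000 students planned and schools allocated 1:1, about 1000 / 2 = 500 waitlist students would have no free-text item. The scaled questionnaire items are collected in both arms.

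5. **Does workshop distress reach the researchers?** Section {22} has facilitators hand students over to school staff. Section {17a} keeps facilitators unaware of which schools are in the trial, so they cannot single out trial participants for a report. Section {20c} does collect reasons why consented students miss a survey or workshop, and section {17b} has the researchers ask why a school or participant leaves the trial. Either could pick up part of it. Neither is an adverse event report, and neither covers a student who is distressed but stays to the end of the workshop.

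**The case against.** The strongest reply is that the three release sections describe delivery of the final dataset, while {21a} implies that one designated researcher looks at responses earlier. As a condensed article, the text may leave the access arrangement to the full protocol. That reading is possible, but no section states it. Section {19} speaks of all data, and the promise of prompt communication makes the silence matter. The sections still have to be reconciled.

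Other objections stand and limit the point:

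- **Open text is an example, not the only route.** The wording of {22} says so, and {21a} covers questionnaire responses in general. A reader might infer that no event could be found in the waitlist arm; the documents support that only for free text.
- **Workshop distress may reach the team in part.** A reader might infer from {11b} that it never does. That sentence concerns the decision to withdraw a student, and {20c} and {17b} may bring some cases to light.
- **The trial is not silent on safety.** A reader might infer that it could support no statement about harm. Depression risk and quality of life are compared between randomised arms (sections {12} and {20a}) and would show average worsening. They do not capture the defined event, which requires attribution to involvement in the trial.
- **Immediate safeguards exist.** Trained facilitators watch for distress, school welfare processes support students, and there is a trial email address. These reduce the consequences of late reading; they do not make the data-flow sections agree.
- **Earlier reading costs some blinding.** Workshop comments come only from intervention students, so anyone who reads them learns the allocation.

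**Conclusion.** The concern holds in three limited parts. First, checking responses, having the ethics committee advise on action and communicating events promptly cannot be delivered under the release arrangements as written. The earliest follow-up free text could wait roughly 16 months, assuming first follow-ups in June 2021 and release in October 2022; the wait is shorter for later respondents and would change with the actual end of collection. Second, free-text detection is unequal by arm, although other responses are collected in both. Third, no route is described for reporting workshop distress to the researchers as an adverse event, and the reasons collected elsewhere cover it only in part.

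This should be fixed, but it does not threaten the trial's main result: randomisation, the primary estimate and its analysis are untouched. The documents do not support the wider conclusions that workshop distress can never come to the team's notice or that nothing could be said about safety.

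**What to change.** 1. Reconcile sections {16c}, {19} and {27} with {21a}, {22} and {23}. State that the data manager sends a free-text extract after each school's follow-up survey to a designated monitor, and that the monitor can ask the data manager to re-identify a student where needed.
2. State that this monitor takes no part in the outcome analysis and does not pass arm-revealing text to the statistician, because the extract discloses allocation. Section {21a} places the monitoring researcher under the biostatistician, who is to stay blinded, so that line of supervision needs a sentence.
3. Add one identically worded item on distress from taking part to the follow-up questionnaire in both arms. Students are not told that the study evaluates the workshop, so the item should ask what the student thinks brought the distress on and should not name the workshop.
4. Use the reasons already gathered under {20c} to record distress-related withdrawals from workshops at trial schools.
5. When reporting, state which sources existed in which arm.

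The cost is one added item, a periodic extract and one unblinded monitor. How an event is handled once found stays with the ethics committee and the schools.

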### Frequency and plans for auditing trial conduct {23}

The principal investigator will meet at least fortnightly with researchers conducting the daily activities of the trial at the coordinating university to discuss and review trial progress, and at least monthly with the full investigator team. Any adverse events or issues in trial progress will be promptly communicated with the investigator team at these meetings or between meetings if necessary. The Advisory Group, comprising experts in male adolescent research and practice, will meet once per year for input into trial progress and will be contacted between meetings as needed. Progress to the trial funder will be reported annually. Any trial protocol amendments will be reported to the Australian and New Zealand Clinical Trials Registry (ANZCTR). No auditing will be undertaken.

### Plans for communicating important protocol amendments to relevant parties (e.g., trial participants, ethical committees) {25}

Any amendments to the protocol will be provided to the Australian New Zealand Clinical Trials Registry and will also be communicated to trial researchers and *Tomorrow Man*.

## Dissemination plans {31a}

Participating schools, students and parents, *Tomorrow Man*, and the funders will be provided with a summary of the findings of the trial. The findings will also be reported in journal articles and presented at scientific conferences and in public forums as requested.

## Discussion

With a focus on improving intentions to seek help by addressing harmful masculine norms, the *Breaking the Man Code* workshops show great promise as a school-based upstream suicide prevention intervention. However, little is known about the effectiveness of interventions such as these for adolescent boys. This trial will fill a gap in the knowledge that is critically needed to inform future interventions with boys and men.

There are some methodological challenges that may be encountered and that may be further complicated by the COVID-19 pandemic. Firstly, schools have been burdened by a need to rapidly adapt to a changing environment. In 2020 in Australia, schools shifted to online learning for students during periods of lockdown. As such, schools may now feel unwilling to take on new activities, such as involvement in research, as they conserve staff energy and resources to manage any further potential upheavals. Parents may likewise be feeling weary of requests for further school-related activities. Consistent with this supposition, recruiting participants for the Consumer Reference Panel in 2020 was unsuccessful. *Tomorrow Man* also adapted the workshop to online delivery during the trial design phase, which introduced a new stratification factor to the trial.

Ethics approvals have been delayed as committees prioritize applications related to COVID-19. This delay meant that when contact with schools begun in October 2020, while ethics approval had been obtained from Monash University’s Human Research Ethics Committee, Department of Education approvals, to undertake research in government schools was still underway. Therefore, only recruitment of independent schools, for whom further ethics approvals were not required, was possible. Approval from the Department of Education in New South Wales has since been received, and applications are underway for Western Australia and Victoria.

In order to mitigate against any potential challenges in working with schools due to COVID-19, the trial was expanded from an initial focus only on schools in Victoria to include schools in New South Wales and Western Australia. Expansion to other locations (South Australia, Queensland, and the Australia Capital Territory) will be considered if school numbers are lower than anticipated in 2021. Schools will be provided with up to A$800 to reimburse them for any administrative costs incurred due to participation in the trial. Further data collection in 2022 has been planned for, should the desired number of schools not be reached in 2021. The funders, Australian Rotary Health and the Medical Research Future Fund, are supportive of the challenges faced by researchers during the pandemic. The trial can be paused or extended if need be.

Despite these potential challenges, the trial is well placed to be completed as per the protocol. Fortunately, the trial design was undertaken as the COVID-19 pandemic unfolded, such that plans to mitigate the impact of the pandemic could be built into the protocol—the pool of potential schools has been increased from one state to three, reimbursement for schools is provided, and data collection into 2022 has been budgeted for. It is also likely that as time goes one school and parents will adapt to the challenges of schooling during a pandemic and may be more receptive to involvement in research.

A gendered approach to suicide prevention is well-overdue and school-based interventions have great potential to foster protective factors in young men. The findings of the trial will be used to improve the workshops for future participants and will also have international relevance to other people designing and implementing suicide prevention interventions for boys and men.

## Trial status

Protocol version 1, 1 April 2021

Recruitment beginning April 2021, to be completed October 2022.
